**Figure 5: Study overview**

The duration of the study is expected to be two years. An overview of all tests performed in the study is illustrated in table 1:

**Table 1: Overview of all tests performed**

| Visit | What                                                         | Duration                 | Notes                         |
|-------|--------------------------------------------------------------|--------------------------|-------------------------------|
| 1     | Screening                                                    | 1 hour                   | Overnight fasted (since 10PM) |
| 2     | Bod Pod
VO 2 max                        | 30 minutes
30 minutes | Overnight fasted (since 10PM) |
| 3     |  H-MRS cycling test                              | 2.5 hours                | 5 hours fasted (since noon)   |
| 4     | 6-hour hyperinsulinemic euglycemic clamp + 2 muscle biopsies | 11 hours                 | Overnight fasted (since 8PM)  |
| 5     | 6-hour hyperinsulinemic euglycemic clamp + 2 muscle biopsies | 11 hours                 | Overnight fasted (since 8PM)  |
| 6     | 6-hour hyperinsulinemic euglycemic clamp + 2 muscle biopsies | 11 hours                 | Overnight fasted (since 8PM)  |

## 4. STUDY POPULATION

### 4.1 Population (base)

In this study 13 Caucasian healthy lean (BMI: 18-25 kg/m^2) male subjects aged 18-40 years will be tested. The study will be restricted to males to prevent hormonal influences of the menstrual cycle and known gender differences in metabolism. Subjects will be recruited in and near the vicinity of Maastricht by means of posters and advertisements on the university and hospital grounds and in local newspapers (see appendix E2 and E3).

Subjects who are interested and respond to the advertisement will be contacted by telephone. During this telephonic interview the study protocol will be verbally explained to the subjects and some of the basic inclusion and exclusion criteria will be checked such as weight, height, BMI, age, sports participation, general health, dietary habits, MRI contra-indications and being vegetarian. By contacting subjects first on the telephone, we can prevent unnecessary travel burden and time effort for the subjects and study personnel. When the subjects are interested and fulfil the basic inclusion criteria, they will receive the detailed subject-information by e-mail or mail accompanied with a general brochure (provided by the Dutch government) about participating in a medical study. Subjects will be instructed to read it carefully, and ask questions when things are unclear. Permission to contact the subject again after one week of consideration will be asked during the telephonic interview. If subjects still want to participate after carefully reading the subject-information and completely understanding it, they will be invited to the university for signing the informed consent immediately followed by a screening visit. Inviting the subjects to the university provides an extra opportunity for the subjects to ask questions to the researcher personally. The informed consent will be signed and dated by the subjects as well as the researchers in duplicate: one form for the researcher and one form for the subjects. Only when the informed consent is signed, subjects will perform the screening measurements. Subjects have the right to end their co-operation to the study at any time.

### 4.2 Inclusion criteria

In order to be eligible to participate in this study, a subject must meet all of the following criteria:

- Caucasian
- Healthy (as determined by responsible physician based on a medical questionnaire)
- Male
- Age: 18-40 years
- Normal BMI: 18-25 kg/m^2
- Stable dietary habits
- No use of medication interfering with investigated study parameters (as determined by responsible physician)

### 4.3 Exclusion criteria

A potential subject who meets any of the following criteria will be excluded from participation in this study:

- Female
- Haemoglobin levels < 7.8 mmol/L
- Uncontrolled hypertension
- Use of anticoagulants
- Engagement in exercise > 3 hours a week
- Being vegetarian or vegan (because of altered whole body carnitine status)
- Smoking
- Alcohol and/or drug abuse
- Unstable body weight (weight gain or loss > 5kg in the last 3 months)
- Significant food allergies/intolerances (seriously hampering study meals)
- Participation in another biomedical study within 1 month before the first study visit, which would possibly hamper our study results
- Medication use known to hamper subject's safety during the study procedures
- Medication use known to interfere with investigated study parameters
- Subjects with contra-indications for MRI
- Subjects who intend to donate blood during the intervention or subjects who have donated blood less than three months before the start of the study
- Subjects who do not want to be informed about unexpected medical findings
- Subjects who do not want that their treating physician is informed

### 4.4 Sample size calculation

The improvement in insulin sensitivity, determined by a clamp (whole body glucose utilization) combined with carnitine infusion is assumed to be around 0.5 mg/kg/min  $\pm$  0.68 mg/kg/min [7, 11-13], therefore  $\mu=0.5$  mg/kg/min. The variation in the individual improvement upon carnitine infusion is estimated to be 0.68 mg/kg/min ( $\sigma=0.68$ ). Using the following online power calculator for cross-over trials

([http://hedwig.mgh.harvard.edu/sample\\_size/js/js\\_crossover\\_quant.html](http://hedwig.mgh.harvard.edu/sample_size/js/js_crossover_quant.html)), sample size was calculated. To reach a power ( $1-\beta$ ) of 80% and a significance level ( $\alpha$ ) of 0.05 (one-sided) a minimal sample size of N=13 was calculated according to the online power calculator. One-sided testing is adequate as the hypothesis will be tested that carnitine *improves* insulin sensitivity.

Considering a drop-out of 20% ( $(13/100)*20 = 3$  subjects) we will need to include 3 extra subjects in the study, so a total inclusion of 16 subjects. Taking into account exclusion after screening in 30% of the cases, we will need to screen 21 subjects.

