## 8. METHODS

### 8.1 Study parameters/endpoints

#### 8.1.1 Main study parameter/endpoint

6-hour hyperinsulinemic euglycemic clamp combined with tracer kinetics and indirect calorimetry:

- Whole body insulin sensitivity measured as GIR in  $\mu\text{mol/kg/min}$  during the stable period of the insulin phase of the clamp.
- Peripheral insulin sensitivity measured as  $R_d$  in  $\mu\text{mol/kg/min}$ .
- Metabolic flexibility (delta RER between basal and insulin stimulated state).

The hyperinsulinemic euglycemic clamp technique is considered the gold standard for assessing insulin sensitivity and metabolic flexibility [15].

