Additional blood samples (7mL) will be drawn at  $t=180$ ,  $t=240$ ,  $t=300$ ,  $t=360$  and  $t=420$  for determination of glucose, FFA, insulin and triglycerides. Between  $t=240$  and  $t=270$  an additional ventilated hood measurement will be performed to assess substrate oxidation. At  $t=480$  a muscle biopsy will be taken in all three intervention arms (LIPID+CAR / LIPID+PLAC / SALINE+PLAC). Thereafter insulin 6,6-D2 glucose, lipid/saline and carnitine/saline infusion will be stopped, while glucose infusion will be continued to prevent hypoglycemia, and subjects will be offered a lunch. An overview of the blood draws taken during the clamp is provided in appendix 2A. An overview of the total amount of blood taken during the entire study is calculated in appendix 2B.

[figure not shown]

Figure 6b: overview hyperinsulinemic euglycemic clamp

De SOP hyperinsulinemic euglycemic clamp is added in appendix K6. The time of insulin administration (6 hours) deviates from the SOP (2.5 hours) due to the additional infusion of Intralipid in this study. Lipid infusion during a clamp is often performed in the metabolic field and also several times before in our research group via the design explained above. As a result of the additional lipid infusion it does not take 2.5 hours to achieve stable glucose values but 6 hours. These six hours are necessary because it takes 3 to 4 hours until insulin resistance occurs regarding glucose infusion rates. The SOP is followed on all the other aspects.

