#### *Metabolic flexibility*

Metabolic flexibility will be computed as the difference in respiratory quotient (RQ) between the basal and insulin stimulate state during the 6-hour hyperinsulinemic euglycemic clamp. The RQ will be computed via  $RQ = \text{vCO}_2/\text{vO}_2$  in which CO2 and O2 are measured via the indirect calorimetry.

To find out whether the time course of insulin sensitivity (whole body glucose infusion rate or RD) is different in the three different treatments (LIPID+Carnitine (treatment A), LIPID+Placebo (treatment B) and Saline+Placebo (treatment C)) a two-way ANOVA for repeated measures is used. Therefore, the dependent variable is “insulin sensitivity”, whilst the two factors are the “conditions” (i.e., three groups: “treatment A”: the Lipid+carnitine, “treatment B”: the Lipid+Placebo, “treatment C”: the Saline+Placebo) and “time”. Post-hoc tests will determine where the significant differences are. The metabolic flexibility ( $\Delta$  RER between basal and insulin stimulated state) will be determined by comparing metabolic flexibility between the conditions with a one-way ANOVA.

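### The 80% power in 4.4 belongs to a one-sided paired test of one carnitine contrast, but 10.1 makes a non-directional three-condition time-course ANOVA with unspecified post-hoc tests the primary analysis

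*Protocol*

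**What the plan says.** **Sample size (Protocol 4.4).** The effect "is assumed to be around 0.5 mg/kg/min". On its spread: "The variation in the individual improvement upon carnitine infusion is estimated to be 0.68 mg/kg/min". The target is 80% power with alpha "0.05 (one-sided) a minimal sample size of N=13 was calculated according to the online power calculator". The direction is defended: "One-sided testing is adequate as the hypothesis will be tested that carnitine" improves insulin sensitivity. With a 20% drop-out allowance, 16 subjects are to be included.

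**Endpoint (Protocol 8.1.1).** The first item is "Whole body insulin sensitivity measured as GIR in" µmol/kg/min, taken in the stable part of the insulin phase. Rd and metabolic flexibility stand beside it.

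**Analysis (Protocol 10.1).** The question put is whether the time course of GIR or Rd differs between LIPID+CAR, LIPID+PLAC and SALINE+PLAC. For this, "a two-way ANOVA for repeated measures is used", with condition and time as factors. Then: "Post-hoc tests will determine where the significant differences are". The general part of section 10 sets significance at p<0.05 and gives no direction.

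**The concern.** The sample-size section and the analysis section describe different tests. Section 4.4 justifies N by one directional comparison of carnitine with no carnitine. Section 10.1 spreads the primary question over three conditions and several time points. Its F-tests have no direction, and the comparison that answers the first primary objective becomes one of several post-hoc results.

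Two things are at stake. First, the stated power may not be the power of the test that is run, so a true carnitine effect of the assumed size could be missed more often than the protocol says. Second, sidedness, contrast and adjustment are left open for the main claim. A significant condition effect could also reflect only the lipid-versus-saline difference that the design deliberately induces.

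**Working it through.** **Inputs.** From 4.4: mean difference δ = 0.5 mg/kg/min, SD 0.68 mg/kg/min, alpha 0.05 one-sided, N = 13, inclusion of 16. From 10.1: three conditions, hence three pairwise comparisons. I read 0.68 as the SD of the within-subject difference, because 4.4 calls it the variation in the individual improvement and because only this reading gives N = 13. Reading it as a within-period SD would need about 23 subjects one-sided.

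**Formula.** Noncentral t with noncentrality (δ/SD)·√n. Degrees of freedom are n − 1 for a paired t-test, or 2(n − 1) if the error is pooled over three conditions. Pooling assumes sphericity, with SD 0.68 for every pair.

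**Reproducing the plan's figure.**
- n = 13: noncentrality (0.5/0.68)·√13 = 0.735 × 3.606 = 2.651; 12 df; one-sided critical value 1.782; power 80.3%.
- n = 12: power 77.1%.

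So 13 is the smallest n that reaches 80%. This identifies the test that was sized.

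**The same contrast under tests compatible with 10.1, n = 13, noncentrality 2.651.**

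| Test of LIPID+CAR vs LIPID+PLAC | df | Critical value | Power |
|---|---|---|---|
| One-sided, unadjusted, paired | 12 | 1.782 | 80.3% |
| One-sided, unadjusted, pooled error | 24 | 1.711 | 82.4% |
| Two-sided, unadjusted, paired | 12 | 2.179 | 68.3% |
| Two-sided, unadjusted, pooled error | 24 | 2.064 | 72.0% |
| Two-sided, Tukey | 24 | 2.497 | 56.8% |
| Two-sided, Bonferroni over three pairs, pooled error | 24 | 2.574 | 53.9% |
| Two-sided, Bonferroni over three pairs, paired | 12 | 2.779 | 47.7% |

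**Sample size for 80% power.** Two-sided unadjusted needs 17 (paired) or 16 (pooled). Bonferroni over three pairs needs 23 (paired) or 21 (pooled).

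**If all 16 included subjects complete.** Noncentrality is 0.735 × 4 = 2.941. Two-sided unadjusted power is 78.5% (15 df) or 81.2% (30 df). Bonferroni gives 60.4% or 65.8%.

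**Omnibus condition test (2 and 24 df).** Its power depends on the saline mean, which 4.4 does not give. Assumed values:
- Saline between the two lipid means or equal to one of them: about 60–73%.
- Saline at least 1.0 mg/kg/min above LIPID+PLAC: over 99%, driven largely by the lipid effect rather than carnitine.

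**Endpoint.** Section 8.1.1 asks for GIR in the stable period. Neither the condition term nor the condition-by-time term of the planned ANOVA is a direct test of that quantity.

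**Rd.** Section 8.3 lists two matching sets of samples, at t=90–120 and at t=450–480. The samples at t=180–420 are listed for glucose, FFA, insulin and triglycerides. As listed, the sets support two Rd levels, basal and insulin-stimulated.

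**The case against.** The strongest reply is that the protocol does not commit to a weaker test. Section 10.1 names no post-hoc method, p<0.05 is silent on direction, and 4.4 says one-sided testing suffices for carnitine. A post-hoc contrast can be directional even though the F-test is not. Run one-sided and unadjusted, it keeps 80–82%. Tukey and Bonferroni appear nowhere in the protocol. With exactly three conditions, unadjusted comparisons after a significant omnibus test are defensible under the usual ANOVA assumptions. The choice of post-hoc procedure is also commonly left to a SAP, which is not at hand. And 13 is a minimum: 16 are to be included, and 8.5 replaces withdrawals.

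Much of this stands, and it makes the lower power figures conditional. It does not remove the mismatch. Section 10 nowhere carries over the one-sided test or names the carnitine contrast as primary, and the current text of 4.4, 8.1.1 and 10.1 does not fit together.

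Two stronger readings are tempting but unsupported:

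- **Dilution over the clamp.** Section 8.3 says "it takes 3 to 4 hours until insulin resistance occurs regarding glucose infusion rates", so a reader might infer that averaging GIR over six hours shrinks the effect and lowers power further. But that sentence concerns the onset of lipid-induced resistance, not of a carnitine effect, and 5.1 cites carnitine effects in three-hour infusions. The SD of a longer average is unknown, and the condition-by-time term could pick up a late effect. The documents give no basis for a diluted power figure.
- **No time factor at all for Rd.** Basal and end-of-clamp Rd give two time levels, enough for a condition-by-time comparison, so this goes too far.

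**Conclusion.** The inconsistency is real. The 80% power in 4.4 is correct for a one-sided 5% paired test of one carnitine contrast, and it is not established for the primary analysis written in 10.1.

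The size depends on a choice the protocol leaves open. With 13 completers, power for the carnitine contrast is 80–82% if one-sided and unadjusted, 68–72% if two-sided and unadjusted, and 48–57% if two-sided and adjusted over three pairs. With 16 completers, the two-sided unadjusted figure is about 78–81%. These figures take δ = 0.5 and SD 0.68 as given, and the pooled-error values also assume sphericity. They describe the pairwise contrast, not the omnibus F-test.

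A reader should not infer that the trial is certainly underpowered. The documents show that the stated power and the stated analysis belong to different tests, and that under ordinary two-sided post-hoc choices the shortfall with 13 completers is material.

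**What to change.** **Preferred.** In 10.1, name one primary test: the LIPID+CAR minus LIPID+PLAC difference in stable-period GIR, one-sided at 0.05 as sized, with a within-subject analysis. Make the time-course ANOVA and the other pairwise contrasts supportive. Say in 4.4 that the calculation refers to this test.

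**Alternative.** If the ANOVA with two-sided post-hoc tests stays primary, restate the power in 4.4 as about 68–72% unadjusted with 13 completers, and lower if the comparisons are adjusted (about 48–57% over three pairs by Tukey or Bonferroni).

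**Either way.** Describe Rd in 10.1 as a comparison of basal with insulin-stimulated values across conditions.

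**Cost.** A paragraph each in 4.4 and 10.1; no extra subjects and no change to the procedures.

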## SUMMARY

**Rationale:** Insulin resistant subjects and type 2 diabetic patients are characterized by a decreased metabolic flexibility: a reduced capability to switch from fat oxidation in the basal state to carbohydrate oxidation in the insulin-stimulated state. This metabolic inflexibility is an early hallmark in the development of diabetes. Recent evidence suggests that a low carnitine availability may limit acetylcarnitine formation, thereby reducing metabolic flexibility. Thus, when substrate flux in the muscle is high, acetyl-CoA concentrations increase, leading to inhibition of pyruvate dehydrogenase (PDH) and thereby reducing glucose oxidation. The conversion of acetyl-CoA to acetylcarnitine relieves this acetyl-CoA pressure on PDH. To provide more direct insight into the effect of carnitine in preventing metabolic inflexibility and insulin resistance and to further explore the mechanism of action is the focus of this research. Here, we hypothesize that the capacity to form acetylcarnitine may rescue lipid-induced insulin resistance. To this end, insulin resistance will be induced by lipid infusion in healthy volunteers and it will be tested whether carnitine co-infusion can alleviate insulin resistance.

**Objective:** The primary objectives are to investigate whether L-carnitine infusion may rescue lipid-induced insulin resistance and whether L-carnitine infusion is improving metabolic flexibility in the state of lipid-induced insulin resistance. Furthermore, a secondary objective is to examine the molecular pathways of carnitine and acetylcarnitine, responsible for muscle insulin sensitivity.

**Study design:** The current study is an interventional randomized crossover trial in which each subject serves as its own control. Subjects will be blinded for the intervention.

**Study population:** n=13, healthy young (18-40 years) male subjects will be included.

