**Visit 4/5/6 (hyperinsulinemic euglycemic clamp):** During visit 4,5, and 6 a 6-hour hyperinsulinemic euglycemic clamp measurement will be carried out. During each visit (visit 4,5,6) a different trial arm will be tested (trial arm 1: LIPID + CAR, trial arm 2: LIPID + PLAC, trial arm 3: SALINE + PLAC). Subjects will be randomly allocated to the different trials arms. Subjects report to the university after an overnight fast (8PM) at 7AM. We will place an intravenous cannula into the forearm, take a blood sample and begin infusing the glucose tracer (this is part of the preperaring steps for the clamp). Next, we will take the first muscle biopsy. Hereafter, we will continue with a 30 minute indirect calorimetry measurement and the 6-hour hyperinsulinemic euglycemic clamp as described in chapter 8.3. At the end of the clamp we will take a second muscle biopsy of the m. vastus lateralis. The test ends and the subject will receive lunch. The subject will be discharged at 5PM provided blood glucose levels are stable. Three days prior to visit 4,5 and 6, the subjects will be asked to withstand from alcohol, refrain from strenuous physical activity and adhere to their normal eating pattern. During these three days, subjects fill out a food diary to monitor if food intake is equal before the test periods (Appendix F2). Furthermore, subjects will be asked to consume a standardized meal the evening before the 6-hour hyperinsulinemic euglycemic test days (visit 4,5,6), followed by an overnight fast (from 8PM). The meal will be a ready to eat meal "macaroni bolognaise" bought in the local supermarket. Visit 4,5 and 6 will be separated by at least two weeks.

An overview of the entire study is provided in figure 5:

[figure not shown]

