### 8.2 Randomisation, blinding and treatment allocation

After inclusion in the study, subjects will be randomly allocated to one of the three interventions arms (saline, intra-lipid, intra-lipid + carnitine). Randomisation will be carried out using an online randomization tool. The intervention arms are labelled according to the subsequent numbers: 1=saline, 2=intra-lipid, 3=intra-lipid+carnitine. The randomisation list is attached in appendix 1A, showing the generated list in excel format. "Set 1" will correspond to the first subject, "set 2" to the second subject and so on. Upon inclusion of a new subject, the subject code will be inserted in consecutive order of inclusion in the excel sheet in the cells that are named "set 1", "set 2" etc.

The leg of the first muscle biopsy of all muscle biopsies will be randomised (left/right). Hereby, potential influence of difference between leg muscle on the outcome will be attenuated. Randomisation will be carried out using an online randomization tool, comparable to the intervention arm randomisation. The legs are labelled according to the subsequent numbers: 1=left leg, 2=right leg. The randomisation list is attached in appendix 1B.

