### **8.5 Replacement of individual subjects after withdrawal**

Subjects will be replaced after withdrawal

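### Section 4.4 applies its drop-out and screening rates to the wrong base (17 included and 25 screened, not 16 and 21), and the randomisation lists stop at 13 sets, with arm codes that conflict with section 3

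*Protocol*

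**What the plan says.** Section 4.4 derives a minimum of 13 subjects for 80% power at a one-sided 5% level. It takes 20% of 13, calls this 3, and concludes that "we will need to include 3 extra subjects in the study, so a total inclusion of 16 subjects". For 30% exclusion after screening it adds that "we will need to screen 21 subjects".

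Other parts of the protocol bear on the same numbers:

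- The Summary gives "n=13, healthy young (18-40 years) male subjects will be included", and section 4.1 also speaks of 13 subjects being tested.
- Section 8.5 reads, in full, "Subjects will be replaced after withdrawal".
- Section 8.2 gives each newly included subject the next set on the list, in order of inclusion. Appendix 1A (treatment order) and Appendix 1B (leg of the first biopsy) both end at Set 13.
- Section 8.2 codes the list as "1=saline, 2=intra-lipid, 3=intra-lipid+carnitine". Section 3 numbers the arms as "trial arm 1: LIPID + CAR, trial arm 2: LIPID + PLAC, trial arm 3: SALINE + PLAC". Section 5.1 also uses arm 1 for lipid with carnitine.

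**The concern.** A drop-out rate is a share of those included, and a screen-failure rate is a share of those screened. Section 4.4 takes each percentage of the number that should remain after the loss, so both allowances come out too small.

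The protocol prints a finite list and a rule for using it, and the two do not fit the stated inclusion. Under the consecutive-order rule the fourteenth subject has no row. The missing orders would have to be produced while the trial runs, and the protocol describes blinding of the subjects only. Pre-generation exists to avoid that. Every subject receives all three conditions, so what is at stake is the order over visits and its protection from choice, not which treatments a subject gets.

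The two numberings agree on 2 and swap 1 and 3. Appendix 1A prints bare numbers without a legend, so a reader who takes them from section 3 would exchange the carnitine day and the saline control day.

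**Working it through.** **Inputs (section 4.4 unless noted).** Effect: it "is assumed to be around 0.5 mg/kg/min". SD of the individual difference: "The variation in the individual improvement upon carnitine infusion is estimated to be 0.68 mg/kg/min". Power 80%, one-sided alpha 0.05, drop-out 20%, exclusion after screening 30%. Appendices 1A and 1B: 13 rows each.

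**1. The base of 13 reproduces.** A one-sided paired t-test with difference 0.5 and SD 0.68 has power 0.803 at n = 13 (0.799 if one further degree of freedom is spent) and 0.771 at n = 12. The 13 is not in dispute.

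**2. The protocol's own inflation.**

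- Inclusion: 13 × 20/100 = 2.6, rounded to 3, and 13 + 3 = 16. Equivalently, 13 × 1.2 = 15.6, rounded up to 16.
- Screening: no formula is printed, but 16 × 1.3 = 20.8, rounded up, gives 21.

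**3. The same rates on the right base.** Required number = target / (1 − rate), rounded up.

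| Step | Calculation | Needed | Stated |
|---|---|---|---|
| Include, for 13 completers | 13/0.8 = 16.25 | 17 | 16 |
| Screen, for 17 included | 17/0.7 = 24.29 | 25 | 21 |
| Screen, if 16 is kept | 16/0.7 = 22.86 | 23 | 21 |

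**4. Forward check.**

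- 16 × 0.8 = 12.8 expected completers, and 17 × 0.8 = 13.6.
- 21 × 0.7 = 14.7 expected inclusions against the 16 wanted. Screening 23 gives 16.1, and screening 25 gives 17.5.
- With independent losses at 20%, the binomial chance of at least 13 completers is 0.60 from 16 included and 0.76 from 17.

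**5. The list against the plan.** Sets 1 to 6 contain each of the six possible orders once, and so do sets 7 to 12. Set 13 is order 2-1-3 again, so that order stands three times and the other five twice. The list is 16 − 13 = 3 rows short of the stated inclusion and 17 − 13 = 4 short of the corrected one, before any further replacement. Appendix 1B is short by the same numbers.

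**6. The codes side by side.**

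| Number | Section 8.2 (list) | Section 3 (trial arm) |
|---|---|---|
| 1 | saline | lipid + carnitine |
| 2 | lipid | lipid + placebo |
| 3 | lipid + carnitine | saline + placebo |

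Section 10.1 adds a third scheme, letters A to C, in the same order as section 3.

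**The case against.** The strongest reply is that section 8.5 makes the inflation almost irrelevant. If withdrawals are replaced, recruitment continues until 13 complete, so 16 and 21 are forecasts. This largely stands. Moving to 17 would not by itself secure 13 completers either (0.76); replacement does that.

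A reader might chain the rates, 21 × 0.7 × 0.8 = 11.8 completers, and infer that power falls below 80%. The protocol does not support this. It sets no stop at 21 screened, states an inclusion of 16, and replaces losses.

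The 13 in the Summary and section 4.1 can also be read as the evaluable target, with 16 as that target plus the allowance. That is reasonable for section 4.1. The Summary's wording is about inclusion, so it is loose and should be aligned, but it is not a deep conflict.

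On the list, the three extra subjects may be the replacements of section 8.5, each taking a withdrawn subject's set. Thirteen rows would then suffice. The protocol does not say so, and section 8.2 read literally gives a new subject the next row. It does not exclude inheritance either, so it would be wrong to assert that a replacement cannot take over a set. Nor can one say that balance over visits would be lost: 13 rows cannot be balanced over six orders in any case, and the list can be extended with the same tool.

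On the codes, section 8.2 defines the list's numbers itself, and nothing applies the section 3 numbers to the list. A mix-up is a risk, not something the plan prescribes.

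**Conclusion.** The point holds in a limited form and should be corrected.

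- **Arithmetic.** The stated figures are wrong at the protocol's own rates, by one subject included and four screened (two if 16 is kept). With replacement in force this affects planning and recruitment more than power.
- **List.** This is the weightier part. Three of the 16 planned inclusions, and any replacement, have no stated source for a treatment order or a biopsy leg. This rests on the consecutive-order rule as written and on the absence of an inheritance rule or reserve rows.
- **Codes.** Numbers 1 and 3 have opposite meanings in sections 8.2 and 3. This is a documentation fault that could cause error in delivery or in analysis coding.

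The size figures assume that 20% and 30% are shares of those included and those screened. The base of 13 is taken as given.

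**What to change.** 1. In section 4.4, divide by one minus the rate and state 13 completers, 17 included and 25 screened. Use the same terms and numbers in the Summary and section 4.1. If the sponsor prefers to keep 16 included, the matching screening number is 23, and the text should say that replacement covers the remainder.
2. In section 8.5, say whether replacements are part of that allowance or come on top of it.
3. Pre-generate Appendices 1A and 1B to at least 18 rows. In 1A this completes a third block of the six orders: keep Set 13 and place the other five orders at random in sets 14 to 18. State which sequence and leg a replacement receives. If replacements come on top of 17 and take new rows, 18 may run out and more are needed.
4. Use one arm code in sections 3, 5.1, 8.2 and 10.1, and print its legend on Appendix 1A.

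The cost is a few corrected figures, a longer list and one added rule. Design and analysis stay as they are; the inclusion and screening numbers become slightly less favourable.
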